### Concealment mechanism {16b}

Intervention allocations (identified by study ID numbers) will be entered into a document and placed in a password protected folder and stored electronically on university-approved servers (i.e., Box).

### Implementation {16c}

The study coordinator and trained research assistants will enroll participants. The study coordinator will verbally inform participants of their intervention allocation following baseline assessments.

## Assignment of interventions: blinding

### Who will be blinded {17a}

The study PI and data analysts will be blinded after assignment to interventions.

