### Outcomes {12}

#### Primary outcomes

Primary outcomes of interest are related to oral health, including image-rated oral mucositis image-rated gingival inflammation and quality of life. We will also capture self-reported oral mucositis and gingival inflammation via survey (using Qualtrics Online Survey Platform [18]). Our target endpoint is 6-months, post-randomization.

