##### Intraoral Imaging

All participants, prior to randomization will undergo an intraoral imaging assessment. Intraoral imaging will be conducted on all study participants at the time of their baseline in-person visit using Mouthwatch® intraoral cameras. Photos of the mouth, teeth, and gums will be captured and saved in individual patient files for research and data purposes only. Images will be captured at 6- and 12-month follow-up assessment visits. We will have a dental consultant review the images and provide summary data. The World Health Organization oral mucositis toxicity scale will be used to assess oral images. The WHO Oral Toxicity Scale rates the anatomical, and function aspects of oral mucositis. The severity of oral ulcers and ability to consume food and liquid is reported on a scale of 0 (no presentation of symptoms) to 4 (not able to tolerate food or liquid diet). Higher scores indicate worse oral mucositis symptomology. To assess gingival inflammation, the Modified Gingival Index will be applied to intraoral images. We will rate inflammation of the gums on a 5-point Likert Scale ranging from 0 (absence of inflammation) to 4(severe inflammation, marked redness, edema. Higher scores indicate more severe inflammation.

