### Procedure for unblinding if needed {17b}

The Study PI and data analysts will remain blinded to the randomization assignments of participants.

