### Plans to promote participant retention and complete follow-up {18b}

Participants receive compensation at each assessment timepoint totaling, $100. Participants will also receive a progress report with detailed feedback from a dental consultant on their oral health (including, baseline and 6-month timepoints).

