### Frequency and plans for auditing trial conduct {23}

Fidelity monitoring is ongoing to assess treatment fidelity. Facilitators whose adherence to protocol is suboptimal will undergo additional protocol training. The study coordinator will meet with the dental consultant a minimum of every 3 months to receive feedback on the quality of intraoral images.

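### The protocol's list of blinded roles omits whoever rates the intraoral images, so two subjective primary outcomes have no stated masking to arm

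*Protocol article*

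**What the plan says.** The Primary outcomes section lists the primary outcomes as "including image-rated oral mucositis image-rated gingival inflammation and quality of life". The first two are read from photographs taken at baseline, 6 and 12 months.

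The Intraoral Imaging section names a reader in general terms: "We will have a dental consultant review the images and provide summary data". For mucositis it names the instrument but not the scorer: "The World Health Organization oral mucositis toxicity scale will be used to assess oral images". For the gums it uses the first person plural: "We will rate inflammation of the gums on a 5-point Likert Scale ranging from 0 (absence of inflammation". Both scales run from 0 to 4 and rest on judgement.

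Blinding is fixed in two places. Item 17a states: "The study PI and data analysts will be blinded after assignment to interventions". Item 17b states: "The Study PI and data analysts will remain blinded to the randomization assignments of participants". Neither names an image rater, and the section on assessor training (item 18a) does not mention masking.

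Three other sections bear on the point:
- Items 16a and 16c: the study coordinator looks up the allocation and tells participants their arm.
- Item 23: "The study coordinator will meet with the dental consultant a minimum of every 3 months to receive feedback on the quality of intraoral images".
- Item 18b: participants receive a "progress report with detailed feedback from a dental consultant on their oral health (including, baseline and 6-month timepoints").

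**The concern.** Item 17a is where a protocol settles who is blinded. Here it gives a positive list, and the list leaves out the role in which masking would protect the image-based primary outcomes. A statistical analysis plan would not normally fill that gap, because masking during outcome assessment is a matter of conduct rather than of analysis.

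Grading redness, swelling or ulcers from a photograph is subjective. A rater who knows the arm may score telehealth participants a little better at follow-up. The bias would then sit in the recorded scores, where a blinded analyst cannot see it or remove it.

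The omission is notable because masking is feasible here. Participants know their arm, so the self-reported quality-of-life outcome cannot be protected in this way. Stored photographs can be.

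**Working it through.** **Step 1: who is masked and who rates.**

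| Role | Stated task | Listed as blinded? |
|---|---|---|
| PI | none stated for image rating, unless included in the first-person wording for the gingival index | yes (17a, 17b) |
| Data analysts | analysis | yes (17a, 17b) |
| Dental consultant | reviews images, provides summary data | no |
| Unnamed raters of the gingival index | apply the index to images | only if they are the PI or analysts |
| Study coordinator | looks up and announces allocation; meets the consultant | no, knows the arm |

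No section of the article lists an image rater, as such, as masked.

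**Step 2: reproduce the design figures.** The inputs come from the Sample size section: d = 0.60, 80% power, α = 0.05, 10% attrition, 50 per arm. I take the test as two-sided, an assumption that reproduces Table 3. The two-sample t-test needs 44.59 per arm, so 45, as in Table 3. Allowing for attrition, 45 / 0.90 = 50. The plan's figures are sound, and 45 per arm is the evaluable number used below.

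**Step 3: illustrate what a differential shift would do.** Suppose there is no true effect, but ratings are shifted by b SD in favour of telehealth. The t statistic then has

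noncentrality = b × √(n/2) = b × √(45/2) = 4.743 × b, with 2 × 45 − 2 = 88 degrees of freedom.

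The rejection probability is P(|T| > critical value). The critical value is 1.987 at α = 0.05. The Statistical methods section plans a Bonferroni adjustment without defining its family. If it covers three primary outcomes (an assumption), the level per test is 0.05 / 3 = 1.7% and the critical value is 2.441.

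| Assumed shift b (SD) | Noncentrality | Error at nominal 5% | Error at nominal 1.7% |
|---|---|---|---|
| 0.1 | 0.474 | 7.6% | 2.9% |
| 0.2 | 0.949 | 15.5% | 7.2% |
| 0.3 | 1.423 | 29.1% | 16.0% |

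The normal approximation gives nearly the same values at 5% (7.6%, 15.8%, 29.6%). For scale, 0.2 SD is 0.2 / 0.60 = one third of the planned effect. The documents give no shift size, so b is assumed throughout. The calculation treats each rating as a continuous score compared by a two-sample t-test, as the sample-size table does.

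**The case against.** The strongest reply is that the article never says a rater is unblinded. Allocations are kept in a password-protected folder, participants carry unique ID numbers, and images are renamed under a procedure that is not shown. The consultant is not described as enrolling participants or delivering the intervention. The full protocol may hold reading rules that the article condenses. All of this stands as a limit on the point, which is that the rater is not listed as masked. It does not remove the point, because item 17a is the article's own list of blinded roles, and the renaming step is not said to hide ID or arm.

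A reader might draw four stronger conclusions that the documents do not support:

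- **That the consultant scores both image outcomes and the blinded roles score nothing.** The wording for the gingival index leaves the scorer open and could include the PI.
- **That the 3-monthly meetings disclose allocation.** Their stated purpose is feedback on image quality. They bring the consultant into contact with someone who knows the arm, and no more than that is stated.
- **That the progress report shows images being scored by identified participant.** The article does not say that the consultant who gives feedback scores the images with identity attached. The reports are not restricted to one arm, so they do not reveal it.
- **That knowing the visit biases the comparison by itself.** Both arms are imaged at the same visits, so a rater who expects improvement at 6 months but does not know the arm shifts both arms alike. Visit matters only together with arm, because knowing both allows differential scoring of change from baseline.

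It is also fair to say that 15.5% is not the planned test's error rate once Bonferroni is applied. The second error column answers that: the absolute rates fall, but the inflation relative to nominal remains.

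**Conclusion.** The point holds as a gap in stated masking. Items 17a and 17b list only the PI and data analysts. Two primary outcomes are subjective image ratings, their rater is not fully identified, and no image rater is listed as masked to arm. Followed as written, the plan leaves those ratings open to an arm-related bias that analyst blinding cannot correct.

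Whether any such bias exists, and how large it is, cannot be known from the documents. The error rates in the working show only how sensitive a trial of this size is to a modest differential shift, under assumed shifts, 45 evaluable per arm, no true effect and, for the second error column, an assumed Bonferroni family of three. The change should be made because the exposure concerns primary outcomes and is cheap to close. If the raters are already masked in practice, a sentence in item 17a saying who they are and how would resolve it.

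**What to change.** 1. In item 17a, name the image rater or raters for each of the two image outcomes and state that they are masked to arm. Make the Intraoral Imaging section agree.
2. Supply images under random codes that carry no study ID or arm, and preferably no date or visit. The existing renaming step can do this.
3. Lock each participant's scores at each follow-up, including 12 months, before that participant's progress report is prepared.
4. State that allocation is not discussed at the 3-monthly image-quality meetings.

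The cost is a coding step and a rule on the order of scoring and reporting. The same rater can serve, and the sample size is unchanged. Progress reports would wait until scores are locked. They support retention, and a 6-month report is promised to participants, so scoring should run in small rolling batches rather than at the end of recruitment; the delay is then slight. Images already stored can be recoded and scored in the same way.

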## Data collection and management

### Plans for assessment and collection of outcomes {18a}

Assessors will undergo research ethics training, subject-matter training (i.e., link between oral and systemic health), trial-specific training (facilitated by the study coordinator)—including mock assessments.

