## Oversight and monitoring

### Composition of the coordinating centre and trial steering committee {5d}

The Trial Steering Committee consists of a postdoctoral fellow who acts as a study coordinator and co-investigator; 3–4 graduate-level research assistants, and 2 clinical personnel (phlebotomist, exercise physiologist).

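### Blinding covers only the PI and analysts, which leaves the dental consultant who reviews the intraoral images and the staff who take them at follow-up free to know the arm

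*Protocol article*

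**What the plan says.** All references are to the protocol article.

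- **Who will be blinded {17a}** states: "The study PI and data analysts will be blinded after assignment to interventions". **Procedure for unblinding if needed {17b}** names the same two roles: "The Study PI and data analysts will remain blinded to the randomization assignments of participants". No other role is listed as blinded.
- **Primary outcomes {12}:** image-rated oral mucositis, image-rated gingival inflammation and quality of life, with a 6-month target endpoint.
- **Intraoral Imaging:** "Images will be captured at 6- and 12-month follow-up assessment visits". A dental consultant reviews the images and supplies summary data. Mucositis and gingival inflammation are each scored from 0 to 4. The section does not say who takes the images, or whether the operator or the consultant is masked.
- **Anthropometrics:** a trained assessor takes height, weight, waist and hip; masking is not mentioned.
- **Plans for assessment and collection of outcomes {18a}:** the training of assessors comprises, among other parts, "trial-specific training (facilitated by the study coordinator"; they also practise in mock assessments. Masking is not mentioned.
- **Sequence generation {16a} and Implementation {16c}:** the coordinator looks up the allocation, and "The study coordinator will verbally inform participants of their intervention allocation following baseline assessments". On enrolment: "The study coordinator and trained research assistants will enroll participants".
- **Composition of the coordinating centre {5d}:** besides the coordinator, "3–4 graduate-level research assistants, and 2 clinical personnel". Assessment and facilitation duties are not assigned.

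**The concern.** Participants and session facilitators cannot be masked in a telehealth trial of this kind. The image rater and the follow-up assessors can be. Item 17a is where the article says who is blinded, and its answer leaves out everyone who produces outcome data.

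The consultant is the most direct route for bias. Grading redness, swelling or ulceration on a short ordinal scale takes judgement, and a rater who knows the arm, or knows that an image comes after the intervention, may grade accordingly. The person who takes the image is a second route, because a rating can reflect only what was photographed.

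A systematic shift between arms from either source looks the same as a treatment effect. Intention-to-treat analysis, baseline adjustment, multiple imputation and the Bonferroni adjustment do not remove it.

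**Working it through.** **1. Reading the roles side by side.**

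| Role | Contact with outcome data | Masking stated |
|---|---|---|
| PI, data analysts | Analysis | Yes (17a, 17b) |
| Dental consultant | Reviews the images | Not stated |
| Staff taking 6- and 12-month images | Produce the images | Not stated |
| Trained assessor | Height, weight, waist, hip | Not stated |
| Study coordinator | Trains assessors; meets the consultant at least every 3 months about image quality | Knows the allocation (16a, 16c) |
| Participants | Self-report | Told their arm (16c) |

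The one person whom the text shows to know the allocation is thus in regular contact with both the assessors and the consultant. The text does not show that either group is told the arm. It shows only that nothing prevents it.

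**2. The plan's own figure.** Sample size {14} gives 45 per arm for d = 0.60, 80% power and α = 0.05. A two-sided two-sample t-test requires n = 44.59, rounded up to 45, with power 80.4%. Allowing for 10% attrition, 45 / 0.90 = 50 per arm. The stated figure reproduces, and this point does not alter it.

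**3. Illustration of what a bias would do.** Inputs: 45 evaluable per arm and α = 0.05, from Sample size {14}; no true effect; a bias b, in SD units, in favour of the telehealth arm. The values of b are assumptions and have no source in the documents.

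Noncentrality = b × √(45/2) = b × 4.743, with 45 + 45 − 2 = 88 degrees of freedom. The two-sided critical value is 1.987 at 5%.

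The Statistical methods section states a Bonferroni adjustment but not the number of tests. For comparison, three tests are assumed, one for each named primary outcome: α = 0.05/3 = 0.0167, critical value 2.441.

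| Assumed bias (SD) | Noncentrality | Type I error, unadjusted 5% | Type I error per outcome, Bonferroni for 3 tests |
|---|---|---|---|
| 0 | 0 | 5.0% | 1.7% |
| 0.1 | 0.474 | 7.6% | 2.9% |
| 0.2 | 0.949 | 15.5% | 7.3% |
| 0.3 | 1.423 | 29.1% | 16.0% |

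The adjustment lowers the absolute rates but does not restore the nominal level: 2.9%, 7.3% and 16.0% all exceed 1.7%.

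**The case against.** The strongest reply has five parts.

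- **Capture is not shown to be free.** Nothing says that operators choose angle, site or retakes as they please. The article describes training with mock assessments, renaming of images under a protocol, and regular feedback on image quality. A detailed capture procedure may well sit in the full protocol. This stands: how much latitude the operator has is unknown, so no claim is made that capture is unstandardised. But none of these steps masks anyone.
- **Staffing.** A reader might infer from the team list that masking needs no additional people. The documents do not support that, because they do not say who facilitates and who assesses. If the research assistants deliver most sessions, separating the roles could be harder. Feasibility with existing staff is plausible, not established.
- **Body measurements.** A reader might put these on a par with the image ratings. They are listed as measures under the secondary outcomes. Height and weight are taken on calibrated instruments and leave little room for influence; waist and hip leave somewhat more. The point is minor here.
- **Error rates.** A reader might take 7.6% to 29.1% as this trial's error rates. They are not: the shifts are assumed, the test is unadjusted, and the article plans Bonferroni.
- **Limited reach.** Quality of life, the outcome behind the sample size, is reported by participants who know their arm. Masking the assessors leaves that as it is.

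These parts narrow the point. They do not answer the central gap: the article states who is blinded, and neither the image rater nor the image takers are among them.

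**Conclusion.** The point holds for the two image-rated primary outcomes. As written, the blinding plan allows the dental consultant and the follow-up image takers to know the arm. It is a design choice stated under item 17a, not merely a detail left to a fuller document. The documents do not show that these people will in fact know the arm, or that bias will occur.

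No size can be derived from the documents. The illustration shows only that, at 45 per arm, a shift of a few tenths of an SD would matter with or without a Bonferroni adjustment. It rests on the assumed shifts, no true effect, a simple two-sample t-test and, for the adjusted column, an assumed three tests.

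The change is worth making because it costs little and because bias that enters when an image is taken cannot be undone afterwards.

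**What to change.** Revise Who will be blinded {17a}, Intraoral Imaging and Plans for assessment and collection of outcomes {18a} to state that:

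1. The dental consultant rates images under coded file names that carry neither arm nor visit. Data management {19} already has images renamed, so this mainly changes the naming rule. The coordinator's meetings with the consultant should not touch on allocation.
2. As far as existing staffing allows, 6- and 12-month images and waist and hip measures are taken by staff who did not facilitate that participant's sessions and have no access to the allocation file.
3. Participants are asked before each follow-up visit not to disclose their arm.

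If full separation proves impossible, say which roles are unmasked.

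**Cost.** Visit booking becomes somewhat less flexible, and access to the allocation folder must be restricted. Because participants receive a progress report with the consultant's feedback on baseline and 6 months, someone other than the consultant must keep the code list and relink the images after rating. That existing staff suffice is an assumption that the sponsor should confirm by stating who facilitates and who assesses. The sample size does not change.

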### Procedure for unblinding if needed {17b}

The Study PI and data analysts will remain blinded to the randomization assignments of participants.

## Data collection and management

### Plans for assessment and collection of outcomes {18a}

Assessors will undergo research ethics training, subject-matter training (i.e., link between oral and systemic health), trial-specific training (facilitated by the study coordinator)—including mock assessments.

### Plans to promote participant retention and complete follow-up {18b}

Participants receive compensation at each assessment timepoint totaling, $100. Participants will also receive a progress report with detailed feedback from a dental consultant on their oral health (including, baseline and 6-month timepoints).

### Data management {19}

Anthropometric data collected from participants will be entered directly into participant file (i.e., paper file). Following this, data will be entered by trained research assistant directly into an electronic datafile stored on secured servers. Oral images will be renamed (per protocol) and downloaded to university-approved servers. Data will be checked by study personnel on a monthly basis to ensure all data is accurately entered and complete.

### Confidentiality {27}

All electronic data will be stored on university-approved secure servers (GU Box). Subjects will be identified by a unique ID number. Links between ID numbers and identifying information, such as telephone numbers, will be password protected. Only study personnel will have access to study data. Data will be directly stored in a database with daily network back-ups.

Blood and saliva samples will be identified with a Unique ID and only evaluated for research purposes. Data linking keys will be stored in a separate database.

All data collection reports and summaries will be kept in a locked file in the Study Coordinator’s office at the research site at Georgetown University’s Lombardi Comprehensive Cancer Center. Data collection instruments will be administered through a HIPPA Compliant online survey platform, Qualtrics.

Standard safeguards to protect the data will be followed. All data will be kept in locked file drawers. Access to data files that contain identifying information will be secured with a password filing system and will be restricted to only approved project staff. All project file cabinets and databases will be secured and locked when not in use.

Audio-recordings of telehealth sessions will be identified by Unique ID, time and date of the session. Audio files will be stored securely on university-approved secure servers (e.g., GU Box).

### Plans for collection, laboratory evaluation and storage of biological specimens for genetic or molecular analysis in this trial/future use {33}

Biospecimens will be transported via private courier and stored at the Lombardi Cancer Center at the Tissue Culture and Biospecimen Resource Shared Resource for processing. Data and specimens will be stored for 10 years after the completion of the primary analyses.

